### Statistical Analysis and Power Analysis

We will present descriptive statistics (eg, proportions, means, SD, and medians) and bivariate correlation measures for variables collected at baseline. To assess the overall effect of the treatment phase (baseline, postintervention, and follow-up) on primary (eg, GD symptom burden, psychological distress, and time spent gaming) and secondary continuous outcome measures, we will conduct repeated measures mixed-effect ANOVA with time as a fixed factor and patient as a random factor; post hoc pairwise comparisons with Bonferroni corrections will be conducted to determine differences in outcome variables across treatment phases. This approach is essentially equivalent to repeated measures ANOVA but will enable us to control individual variability and perform analyses including all cases provided each patient has 1 valid pre- or postoutcome value. In addition, we will conduct logistic mixed-effect model analyses to assess the effect of time on binary outcome measures (ie, symptom improvement).

All tests will be 2-sided with the α level set at .05. Based on previous CBT-based therapy studies for GD that indicate medium-to-large effect sizes from pre- to posttest for symptom burden, time playing, and mental health improvement [32], we estimate that a minimum of 28 participants would be required to achieve 80% power to detect such differences across all outcome measures (Cohen *f*=0.25). To accommodate a potential attrition rate of 30%, we will enroll a minimum of 37 participants for quantitative analyses. Follow-up univariate logistic regressions will be conducted to explore which baseline characteristics are predictive of participant symptom improvement, defined by subcutoff scores for the GDT, IGDS9-SF, and CORE-OM 34 follow-up. Planned analyses will be conducted apropos of missing data patterns and modified accordingly when needed. The results will be reported as means and odds ratios, respectively, with 95% CIs.

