## Discussion

### Principal Findings

This study will evaluate the effectiveness and acceptability of psychological treatment for patients with problematic gaming behavior and GD about symptoms of GD and psychological distress and time spent gaming. This study will be a 1-group, pretest-posttest with a follow-up design including at least 37 patients undergoing psychological treatment at an outpatient clinic specialized in GD. The treatment is module-based and is based on CBT and FT. The treatment will be given as individual sessions with the patient sessions, family sessions, sessions with parents, or a combination of the three. The duration of the therapy provided to each patient can vary, ranging from 5 to 20+ sessions based on the case formulation of the patient and the progression of the therapy.

This study is important in several aspects: this study has a high external validity since it is conducted in routine care. Due to that, this study ensures that the results are relevant for a diverse clinical population with patients with high comorbidity with other psychiatric conditions. The treatment consisting of standard CBT and FT interventions not only roots this study in well-established therapeutic techniques but also indicates that, should the results be positive, the treatment protocol can easily be adopted by other clinics. Moreover, this study’s origins in actual clinical practice underscore its commitment to real-world effectiveness, emphasizing the value of learning directly from clinical experiences and spreading that knowledge.

There are feasibility and exploratory elements to this study. The patients answer questions about satisfaction and working alliance with the therapist at the posttreatment assessment. There are also planned qualitative interviews with the patients and relatives of the patients regarding their view of the treatment, important components of the treatment, if anything should change, and the patient-clinician relationship.

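### The 30% attrition allowance is miscalculated: 28 required participants need 40 enrolled, and the stated minimum of 37 covers only about 24% attrition

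*Protocol article*

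**What the plan says.** In the protocol article, section Statistical Analysis and Power Analysis, the sizing runs in two steps.

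- Required number: "we estimate that a minimum of 28 participants would be required to achieve 80% power", the target being to "detect such differences across all outcome measures (Cohen *f*=0.25"). On the significance level: "All tests will be 2-sided with the α level set at .05".
- Allowance for loss: "To accommodate a potential attrition rate of 30%, we will enroll a minimum of 37 participants for quantitative analyses".

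The Discussion, under Principal Findings, repeats the enrolment figure as a feature of the design: "including at least 37 patients undergoing psychological treatment at an outpatient clinic specialized in GD".

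The same statistical section describes the analysis. The main model tests the "overall effect of the treatment phase (baseline, postintervention, and follow-up"), which is three occasions in one group. It is a mixed-effect model with patient as a random factor, chosen in part because it can "perform analyses including all cases provided each patient has 1 valid pre- or postoutcome value". The article gives no other attrition rate and no other method of inflating the sample.

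**The concern.** Three printed figures (28 needed, 30% lost, 37 enrolled) cannot all be true together. The likely cause is a common slip: 30% of the required number was added, where 30% of the enrolled number should have been allowed for.

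The figure matters because 37 is the only quantitative enrolment minimum in the article, and recruitment will be judged against it. A study that enrolled 37 to 39 patients and lost the anticipated 30% could report its minimum as met while holding fewer than the 28 it says it needs. The Sample Size section makes enrolment depend on how many patients come to the clinic, and Limitations and Strengths reports recruitment challenges. Finishing close to the minimum is therefore a real possibility.

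**Working it through.** **Inputs from the article** (Statistical Analysis and Power Analysis): required n = 28, power 80%, f = 0.25, two-sided α = 0.05, three occasions (m = 3), one group, attrition d = 0.30, minimum enrolment 37. **Assumed, because not stated:** correlation between occasions ρ = 0.5, and sphericity.

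**Step 1. Reproduce the 28.** For a one-group repeated-measures ANOVA the noncentrality is λ = f² × n × m/(1 − ρ), with m − 1 and (n − 1)(m − 1) degrees of freedom. At n = 28, λ = 0.0625 × 28 × 3/0.5 = 10.5 on 2 and 54 df.

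| n | λ | Power |
|---|---|---|
| 25 | 9.375 | 76.1% |
| 26 | 9.75 | 77.9% |
| 27 | 10.125 | 79.6% |
| 28 | 10.5 | 81.2% |

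The smallest n that reaches 80% is 28, so the plan's first figure reproduces. This does not prove that ρ = 0.5 was the planners' value: two occasions with ρ = 0.6 also give 28.

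**Step 2. Reproduce the 37.**

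- Dividing attrition out: 28/(1 − 0.30) = 40.
- Adding 30% to the required number: 28 × 1.30 = 36.4, rounded up to 37.

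Only the second gives the printed figure. The gap is 3 patients, too large for rounding.

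**Step 3. What 37 delivers.**

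- Remaining after 30% loss: 37 × 0.70 = 25.9, against 28 required.
- Attrition that 37 can absorb: 1 − 28/37 = 24.3%.
- Check of 40: 40 × 0.70 = 28.

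Steps 2 and 3 use only the article's own numbers.

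**Step 4. Power if only completers count.** From the table, 25 or 26 completers give 76.1% or 77.9%. These percentages move with the assumed correlation: at n = 26, power is 69.7% for ρ = 0.4 and 86.8% for ρ = 0.6.

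**Step 5. Power under the planned mixed model.** This is an approximate generalised least squares calculation for 37 enrolled and 30% dropout, with f = 0.25, compound symmetry, ρ = 0.5 and ignorable missingness. Dropouts contribute the occasions they attended.

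| Shape of change | All lost before posttreatment | Half before, half after | All lost after posttreatment |
|---|---|---|---|
| Linear over the three occasions | 81.1% | 82.3% | 83.4% |
| Change by posttreatment, then held | 82.2% | 86.1% | 89.1% |
| Change by posttreatment, then lost | 78.9% | 84.9% | 89.1% |

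The range is about 79% to 89%. Only one of the nine cases falls below 80%.

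**The case against.** A reader might infer that the trial, as planned, will not reach 80% power. The documents do not support that. The 76–78% treats every lost patient as contributing nothing, whereas the stated analysis retains anyone with one valid value, and step 5 puts its power at about 80% or above in most scenarios. The completer figures also rest on a correlation and a sphericity condition that the article does not give.

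Two further points can be made for the plan. First, 37 is a floor: all patients who come to the clinic for treatment are invited, recruitment closes on a calendar date, and nothing stops enrolment at 37. The shortfall arises only if enrolment ends at 37 to 39 and attrition reaches the full 30%. Second, the study describes itself as exploratory and has a single arm, so three patients on a minimum change no analysis, outcome or eligibility rule.

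All of this limits the consequence, but none of it repairs the arithmetic. The article does not use partial data to justify 37; it presents 37 as the number that accommodates 30% attrition, which it does not. A minimum is also the number that ought to suffice on its own terms. Nor can condensation into an article explain the gap, since all three figures are printed and a fuller document could not make 37 × 0.70 reach 28.

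**Conclusion.** Wrong as written. At 30% attrition, 28 required participants imply a minimum enrolment of 40; the stated 37 leaves about 26 and covers about 24% attrition. This conclusion is certain, because it uses only the article's own figures.

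The power consequence is limited to the plan's completer-based sizing: a loss of about 2 to 4 points against 80%, conditional on ρ = 0.5 and sphericity. Under the planned mixed model the loss may largely or wholly disappear, given ignorable missingness and depending on when patients leave and how the outcome moves. It is a minor to moderate correction of a stated figure and does not undermine the design.

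**What to change.** Restate the minimum enrolment as 40 in Statistical Analysis and Power Analysis and under Principal Findings. If 37 is to stay, one of the following would make the text consistent:

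- say that 37 allows for about 24% attrition; or
- justify 37 at 30% attrition explicitly by the mixed model's use of partial data, stating the assumed correlation, dropout timing and shape of change.

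The first option changes one number in two places and raises the recruitment floor by three patients. The second is a change of wording, and the third also needs a short power calculation. None alters the outcomes, the analysis model or the recruitment window.

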### Additional Measures

Data concerning demographics, what games they are playing, everyday gaming behavior, social life, family life, psychical health, sleep and eating habits, as well as symptoms of ASD and ADHD, are gathered at baseline to provide a comprehensive picture of the treatment-seeking sample. For the adults, ASD symptoms will be measured with Ritvo Autism and Asperger Diagnostic Scale 14 [61]. Symptoms of ADHD will be measured by the Adult ADHD Self-Report Scale part A, which contains 6 items, and it has been found that these questions are the most predictive of ADHD [62]. For children, patient-reported symptoms of ASD and ADHD are measured with Ritvo Autism and Asperger Diagnostic Scale 14 and Adult ADHD Self-Report Scale, respectively. Likewise, parent-reported child ASD and ADHD symptoms are measured using the Autism Quotient [63] and Swanson, Nolan, and Pelham [64] scales, respectively. After each treatment session, the patients will answer 4 questions: rating their psychological well-being on a 1-10 scale, reporting how much time they have spent gaming the last week, rating how much their psychological distress depends on their gaming on a scale of 1-10, and the reporting of how helpful they found this treatment session on a 1-10 scale. After treatment, the patients will be asked whether they have received any parallel interventions during the treatment and whether they will seek further help for their problems. Before treatment begins, the patients’ current medications will be documented. During the posttreatment assessment, any changes to their medications during the treatment will be recorded. These changes will be reported at the group level in the final paper.

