### Dissemination

Findings will be published in peer-reviewed journals, at research conferences, and disseminated to the general public.

This study will be reported per the Transparent Reporting of Evaluations With Nonrandomized Designs statement. The primary objective is to compose a key scientific paper concentrating on the efficacy and acceptability of the treatment. Subsequent studies within the research project will include qualitative interviews and analysis to explore the experiences of both patients and their relatives with the treatment. Additional papers may also emerge, delving into predictors and moderators influencing treatment outcomes.

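### The predictor screen is open-ended, uncorrected and sized at a floor of 26 to 37 patients: chance predictors are likely if the whole baseline pool is tested, and uncommon yes/no traits will often have no finite odds ratio

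*Protocol article*

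**What the plan says.** The relevant text is in Statistical Analysis and Power Analysis.

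- **Method:** "Follow-up univariate logistic regressions will be conducted to explore which baseline characteristics are predictive of participant symptom improvement". These are one-predictor models. No list of predictors is given.
- **Outcome:** improvement is "defined by subcutoff scores for the GDT, IGDS9-SF, and CORE-OM 34 follow-up". The sentence can mean one composite status or three separate statuses.
- **Error rate:** "All tests will be 2-sided with the α level set at .05".
- **Correction:** the only one named is for another step: "post hoc pairwise comparisons with Bonferroni corrections will be conducted to determine differences in outcome variables across treatment phases".
- **Reporting:** odds ratios are promised with 95% confidence intervals.
- **Size:** "we estimate that a minimum of 28 participants would be required to achieve 80% power to detect such differences across all outcome measures". This is raised to a minimum of 37 for 30% attrition. The number concerns change over time, not prediction.

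The pool of candidates is wide. Additional Measures lists "Data concerning demographics, what games they are playing, everyday gaming behavior, social life, family life, psychical health, sleep and eating habits", plus autism and ADHD symptoms, and Table 1 ticks a further 13 measures at baseline. Under Dissemination the article adds: "Additional papers may also emerge, delving into predictors and moderators influencing treatment outcomes".

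**The concern.** Two separate things can go wrong.

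1. **Chance findings.** When many characteristics are tested one at a time at .05 in a small sample, some may reach significance although none predicts anything. The article does not say how many will be tested or that all will be reported, so a reader of the results could not judge how surprising a significant predictor is.
2. **Odds ratios that cannot be estimated.** If every patient with a given trait improved, or none did, one cell of the two-by-two table is empty. The maximum-likelihood odds ratio is then zero or infinite and its Wald interval carries no information. If nobody has the trait, there is no estimate at all. The promised odds ratio with a 95% interval cannot be given.

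At stake is the credibility of any statement about which patients improve. The main estimates of change over time are not affected.

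**Working it through.** **Sample size.** The plan's 28 reproduces for a repeated-measures ANOVA with f = 0.25, three occasions, alpha .05, sphericity and a correlation of 0.5 between occasions (my assumption; the article gives none): power is 0.812 at 28. The enrolment figure follows from 28 × 1.3 = 36.4, rounded up to 37. With 30% lost, 37 × 0.7 = 25.9, so about 26 remain. The screen therefore has 26 to 37 patients at the planned minimum. CORE-OM 34 appears in Table 1 (age 16 and over) but not in Table 2 (13 to 15 years), so that outcome has fewer still if any younger patients enrol at that minimum.

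**Size of the pool (my count).** Additional Measures gives 10 domains: demographics, games played, gaming behaviour, social life, family life, health, sleep, eating, autism symptoms and ADHD symptoms. Table 1 gives 13 more with a baseline tick: CORE-OM 34, GDT, IGDS9-SF, gaming time, MINI, GAF, gambling screen, social media, motives, emotion regulation, alcohol, substances and harm. The total is 23. Counting the seven motives and five harm areas singly gives 23 − 2 + 7 + 5 = 33.

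**Chance findings with no true predictor.** Expected number = tests × level. Chance of at least one, if tests are independent, = 1 − (1 − level)^tests.

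| Reading | Tests | Expected at 5% | Chance of at least one |
|---|---|---|---|
| 10 predictors, composite | 10 | 0.5 | 40% |
| 23 predictors, composite | 23 | 1.15 | 69% |
| 33 predictors, composite | 33 | 1.65 | 82% |
| 23 predictors, three outcomes | 69 | 3.45 | 97% |

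Correlation between tests lowers the last column but not the expected number. With 26 patients, predictors correlated 0.3 and the scores behind the three outcomes correlated 0.5, a simulation of the 69-test case gave 3.46 expected and 92%.

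**True level of the tests.** Simulated one-predictor models under the null gave a Wald type I error of about 0% to 4% at 26 patients and 0% to 5% at 37. Likelihood-ratio tests ran at about 3% to 8%. Taking 2% to 3.5% as typical for Wald tests:

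- 69 tests: 69 × 0.02 = 1.4 to 69 × 0.035 = 2.4 expected.
- 23 tests: 23 × 0.02 = 0.5 to 23 × 0.035 = 0.8 expected. The chance of at least one is 1 − 0.98^23 = 37% to 1 − 0.965^23 = 56%.

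**Empty cells.** Let q be the share of patients with the trait, p the share improving (no association), and k the number with the trait, Binomial(n, q). Given k from 1 to n − 1, no cell is empty with probability [1 − p^k − (1 − p)^k] × [1 − p^(n−k) − (1 − p)^(n−k)]. For k = 0 or n the odds ratio does not exist. Averaging over k and subtracting from 1 gives the table below. The article gives neither q nor p; both are assumed.

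| n | q | p = 50% | p = 70% | p = 85% |
|---|---|---|---|---|
| 26 | 15% | 25% | 34% | 58% |
| 26 | 20% | 13% | 22% | 48% |
| 37 | 15% | 11% | 20% | 44% |
| 37 | 20% | 4% | 10% | 33% |

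Simulation over improvement rates of 20% to 80% shows where the problem stops. A continuous predictor was inestimable in 0% to 1% of runs. A yes/no trait held by half the patients was inestimable in 0% to 13% at 26 and 0% to 4% at 37. At 70 patients, a trait held by 10% still failed in 6% to 26%.

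**The case against.** The strongest reply is that the step is exploratory. The article words it so, prediction is not among the stated objectives, and predictor papers are only a possibility. Uncorrected testing is accepted in exploratory work, and a journal article may leave the predictor list and the estimator to an analysis plan. Much of this stands. It removes any charge of a false confirmatory claim and any case for compulsory family-wise correction. It does not remove the point, because the article itself fixes the level for all tests, the model type and the report format, and it singles out one other step for correction.

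A reader might infer that every baseline characteristic will be tested against three outcomes in 26 to 37 patients, so that 3.5 false predictors and a near-certain chance finding follow. The text does not support this:

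- It never says every characteristic. Additional Measures describes its data as there to characterise the sample.
- Three outcomes is one reading; a composite is another.
- 37 is a minimum, and recruitment depends on how many patients seek treatment.
- Wald tests run below 5% at this size. An empty cell inflates the standard error, so under Wald testing it tends to hide a trait rather than name it as a predictor. With Wald tests in the 69-test case at 26 patients, 300 simulated runs gave 2.0 expected hits and a 79% chance of any when all predictors were continuous. With 10 of the 23 predictors binary at 18% prevalence, they gave 0.9 to 1.6 hits and 46% to 72%.

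Nor are inestimable odds ratios to be expected across the battery, since much of it consists of scale scores.

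**Conclusion.** The point holds in limited form. The screen has no stated bound on its pool, no correction, an ambiguous outcome and a floor of about 26 retained patients. If all 23 domains were tested at a true 5% level, with independent tests for the probabilities, 1.2 chance predictors (69% chance of at least one) would be expected for a composite and 3.5 (97%) for three outcomes. These are upper-end figures for that pool, and Wald testing or a shorter list brings them down.

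The firmer part is estimation. For yes/no traits held by 15% to 20% of patients, with 50% to 85% improving, an empty cell has probability 13% to 58% at 26 patients and 4% to 44% at 37. The battery contains items that could be this uncommon: single MINI diagnoses, the gambling screen and single substances. For these, ordinary logistic regression would often fail to give the promised odds ratio and interval. This concerns an exploratory secondary analysis and should be put right before the data are analysed.

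**What to change.** In Statistical Analysis and Power Analysis:

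1. Fit the predictor regressions with Firth's penalised likelihood and profile-likelihood 95% confidence intervals. This gives finite odds ratios when a cell is empty, provided the trait and the outcome both vary.
2. State whether improvement is one composite or three outcomes, and which age group each regression covers, since CORE-OM 34 is not collected below age 16.
3. Put first a short list that the Introduction supports: escape and coping motives, psychiatric comorbidity, ADHD and autism symptoms, and family relations. The Introduction links these to gaming disorder rather than to treatment response, so this sets priority and is not evidence of prediction.
4. Report every characteristic tested, with its estimate and interval, and the number of tests.
5. Label the results hypothesis-generating. False-discovery-rate adjusted p values may be shown alongside.

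Holm or Bonferroni should not be required. Over 69 tests Bonferroni means .05 / 69 = .0007. At 50% improved, the odds ratio per standard deviation detectable with 80% power then rises from about 3.0 to 5.2 at 26 patients and from about 2.5 to 4.0 at 37. Holm starts at the same threshold.

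The cost is wording and standard software, with no new data. Odds ratios will be slightly shrunken and fewer characteristics will be presented as predictors.

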### Eligibility Criteria

This study aims to conduct a naturalistic effectiveness trial designed to include a representative group of patients; hence, inclusion and exclusion criteria are minimal. The inclusion criteria for participation include (1) being aged 13 years or older; (2) seeking treatment for problematic gaming behavior or GD as a patient or as a parent on behalf of their child; and (3) the patient’s gaming is affecting their well-being, daily functioning, or creating conflicts in the family.

The exclusion criteria for participation are (1) somatic or psychiatric disease that is contraindicating or severely complicates the implementation of the intervention (eg, ongoing psychotic, manic episode, or neuropsychiatric condition with severe disability) and in which case the patient is referred on from the clinic, and (2) the patient or parent (if the patient is aged younger than 15 years) is not able to read and communicate proficiently in Swedish.

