#### Adults

Symptoms of GD are measured with both the Gaming Disorder Test (GDT) [45] and the Internet Gaming Disorder Scale–Short-Form (IGDS9-SF) [46]. The GDT consists of 4 questions that cover the criteria for GD in *ICD-11* and is answered on a 5-point Likert scale, from 1 to 5. The total score is 20 and the suggested cutoff is that all questions are answered with 4 or 5. The IGDS9-SF consists of 9 questions that cover the criteria for IGD in the *DSM-V*, with an additional question added about craving, and is answered on a 5-point Likert scale, from 1 to 5. The total score for the original IGDS9-SF questions is 45. The suggested cutoff point based on an Italian clinical sample is 21 [47]. Psychological distress is measured by the Clinical Outcomes in Routine Evaluation–Outcome Measure 34 questions (CORE-OM 34). The CORE-OM 34 contains 34 questions about subjective well-being, symptoms (anxiety, depression, and physical problems), life functioning, and risk of suicide [48]. It is answered on a 5-point Likert scale, from 1 to 5. The last primary outcome measure is how much time the patient has spent on gaming in the last week, where the patient themselves approximates how much time they have spent gaming.

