#### Children

Symptoms of GD are measured with the GDT, IGDS9-SF, and Gaming Addiction Identification Test [49]. The Gaming Addiction Identification Test is a parent assessment with 17 questions that is answered on a 5-point Likert scale, from 1 to 5. It also contains a question about the estimated time spent gaming per day. Psychological distress is measured by the Revised Child Anxiety and Depression Scale (RCADS) [50] child and parent self-report. The RCADS contains 47 items assessed on a 5-point Likert scale, from 1-5, for children and parents, covering subscales for social phobia, panic disorder, general anxiety disorder, obsessive-compulsive disorder, separation anxiety, and depression. Scores are compiled into 2 totals: one for combined anxiety and depression, and another for exclusively anxiety-related symptoms. The RCADS is globally recognized in research and clinical settings for its strong psychometric reliability [50]. Lastly, the children estimate how much time they have spent gaming during the last week.

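### Symptom improvement is defined as being below cutoff at follow-up, with no condition on baseline status, so a patient who enters below cutoff and does not change is labelled improved; ages 13-15 also lack one of the three scales

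*Protocol article*

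**What the plan says.** The section Statistical Analysis and Power Analysis uses a binary improvement outcome in two analyses.

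- Predictors: "Follow-up univariate logistic regressions will be conducted to explore which baseline characteristics are predictive of participant symptom improvement". The same sentence goes on to define the outcome: "participant symptom improvement, defined by subcutoff scores for the GDT, IGDS9-SF, and CORE-OM 34 follow-up".
- Change over time: "logistic mixed-effect model analyses to assess the effect of time on binary outcome measures (ie, symptom improvement").

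Under Eligibility Criteria, the article says that "inclusion and exclusion criteria are minimal". Patients qualify if they are 13 or older, are "seeking treatment for problematic gaming behavior or GD as a patient or as a parent on behalf of their child", and their gaming affects well-being, "daily functioning, or creating conflicts in the family". No GD diagnosis and no GDT, IGDS9-SF or CORE-OM 34 score is required.

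Under Primary Outcome Measures, Adults, the GDT has four items scored 1 to 5, and "the suggested cutoff is that all questions are answered with 4 or 5". The IGDS9-SF cutoff is 21 of 45. CORE-OM 34 is the adult distress scale (16 and older, Table 1). For ages 13-15 the Children subsection says "Psychological distress is measured by the Revised Child Anxiety and Depression Scale (RCADS"), and Table 2 does not list CORE-OM 34.

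**The concern.** Improvement implies movement from a worse state to a better one. The stated rule looks only at the end state, and the entry criteria do not guarantee the worse starting state. Three things follow.

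1. Patients who were below cutoff throughout are counted with those who crossed it.
2. The predictor regressions are univariate, so nothing in them separates response from low severity at entry. Any characteristic correlated with mild baseline symptoms may appear as a predictor of response. The Dissemination section foresees papers on predictors and moderators, so this could reach print.
3. The rule names a scale that the youngest patients do not complete, and it does not say whether the three scales are combined.

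In the logistic mixed model the term is also awkward, because improvement does not exist as a state at baseline.

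**Working it through.** **Plan's own figure.** The article gives no expected improvement rate, so there is none to reproduce. The only related figure is the minimum of 28 participants for the repeated-measures analysis. It reproduces with a noncentral F, λ = f²·n·m/(1−ρ), f = 0.25, m = 3 time points and an assumed ρ = 0.5: n = 28, power 0.8125. The point here does not depend on it; 28 serves only to turn shares into patient counts.

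**Step 1: can an unchanged patient be labelled improved?** Enumerating all GDT answer patterns against the stated cutoff:

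- highest total that is below cutoff: 5+5+5+3 = 18
- lowest total that meets it: 4+4+4+4 = 16

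A patient at 18 of 20 is therefore below cutoff, may enter the study, and is labelled improved on the GDT if still at 18. A move from 4,4,4,4 to 4,4,4,3 is also improvement.

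**Step 2: effect on the labelled rate.** Let b be the share below cutoff at entry (assumed to stay below) and r the share of the others who cross. Labelled rate = b + (1−b)·r. The documents do not give b or r; the values are assumptions.

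| b | r | Labelled improved | Already below, among those labelled | Above cutoff at entry, of 28 |
|---|---|---|---|---|
| 0.1 | 0 | 10% (2.8 of 28) | 100% | 25.2 |
| 0.5 | 0 | 50% (14.0 of 28) | 100% | 14.0 |
| 0.1 | 0.3 | 0.1 + 0.9×0.3 = 37% | 0.10/0.37 = 27% | 25.2 |
| 0.5 | 0.3 | 0.5 + 0.5×0.3 = 65% | 0.50/0.65 = 77% | 14.0 |

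Among patients who could improve, the rate is 0% in the first two rows and 30% in the last two.

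**Step 3: how large might b be?** A simulation with assumed inputs (items with latent SD 1, common-factor share 0.5, rounded and clipped to 1-5; below the IGDS9-SF cutoff taken as a total under 21):

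| Mean GDT item | Below GDT cutoff | Below GDT and IGDS9-SF, equal item means | Below both, IGDS9-SF items one point lower |
|---|---|---|---|
| about 3.5 | 80% | 5% | 38% |
| about 3.9 | 60% | 1% | 16% |

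The IGDS9-SF cutoff is much laxer (21/9 = 2.33 per item), so a joint rule shrinks b sharply, and adding CORE-OM 34 can only lower it further. The article does not say which rule applies.

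**Step 4: predictor regression with no treatment effect.** Baseline and follow-up scores are bivariate normal with the same cutoff at both visits and correlation ρ (assumed). OR = [p₁/(1−p₁)]/[p₀/(1−p₀)], where p₁ and p₀ are the chances of being below cutoff at follow-up for patients below and above it at baseline.

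| ρ | Share below at entry | p₁ | p₀ | OR |
|---|---|---|---|---|
| 0.7 | 0.2 | 0.564 | 0.108 | 10.7 |
| 0.7 | 0.3 | 0.634 | 0.156 | 9.4 |
| 0.5 | 0.2 | 0.434 | 0.141 | 4.7 |
| 0.5 | 0.3 | 0.521 | 0.205 | 4.2 |

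If nobody changes at all, the prediction is perfect.

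**Step 5: ages 13-15.** With a joint rule, CORE-OM 34 is never available, so no child can be classified. With separate rules, children keep the GDT and IGDS9-SF outcomes and have no binary distress outcome.

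**The case against.** The strongest reply is that this concerns an exploratory outcome. The primary outcomes are analysed as continuous measures over baseline, post-treatment and follow-up, and none of that is touched. The article reports means and odds ratios and names no improvement proportion as an endpoint. In the logistic mixed model the workable reading is cutoff status at each visit; on that reading a patient below cutoff throughout contributes no apparent change. Status at follow-up is a legitimate outcome, so the fault lies largely in the word improvement. All of this stands, and it limits the severity.

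It can also be said that how the scales are combined, and the RCADS threshold, belong in an analysis plan. That is fair for the detail. It does not cover the definition itself, which the article states and which, if followed, mislabels patients.

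Two stronger readings are tempting and not supported. A reader might infer that 60% to 80% of patients would count as improved before treatment starts. That needs the GDT applied alone and item distributions that the document does not give; under a joint rule with equal item means the same model gives about 1% to 5%. A reader might also infer that children drop out of the analysis altogether. That needs the joint rule, so the two inferences cannot both hold.

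**Conclusion.** The point holds in limited form. The stated definition, taken with entry criteria that set no score or diagnosis, labels patients who enter and stay below cutoff as improved, and the unadjusted regressions will tend to report low baseline severity as a predictor of improvement. The odds ratio of about 4 to 11 with no treatment effect rests on assumed correlations of 0.5 to 0.7 and on 20% to 30% being below cutoff at entry. The number of patients affected cannot be found from the document: a few percent or a majority are both possible, depending on severity at entry and on whether the scales are combined. For ages 13-15 the rule is unusable (joint) or leaves distress without a binary outcome (separate). The damage is confined to the predictor regressions and to the meaning of the binary outcome.

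**What to change.** Settle the wording before the data are analysed, so that results cannot guide the definition.

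1. Either define improvement per instrument, among patients above that instrument's cutoff at baseline; or call the outcome below cutoff at follow-up and adjust each predictor model for the baseline score of that instrument.
2. Make above or below cutoff status at each visit the outcome of the logistic mixed model.
3. Use the RCADS in place of CORE-OM 34 for ages 13-15.

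All of this uses measures already scheduled at baseline and follow-up. The cost of the first option is a smaller denominator: 28×(1−b), that is 25.2 patients at b = 0.1 and 14.0 at b = 0.5. If a large share enters below the strict GDT cutoff, little would remain on that scale. The second option keeps everyone and costs one covariate. A reliable change criterion could be added, but it is optional.
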